**6.7. Clinical Protocol:**

Frequency of treatment: Three sessions of desensitizing treatment will be done, with a 24-hour interval between sessions.

**6.7.1. CPP-ACPF and Placebo**

The subjects of G. CPP-ACPF will receive the application of the MI Paste Plus ™ gel (Recaldent ™, GC América, United States) on the vestibular surfaces of hypersensitive teeth with the aid of a Microbrush applicator (Microbrush, 3M ESPE, São Paulo, Brazil) and was maintained undisturbed for 5 min. A rubber cup mounted on a low speed handpiece will then be used to scrub the desensitizing gel for 20 seconds on each tooth as per the manufacturer's specification (http://www.mi-paste.com/apply.php) . After application of the CPP-ACPF dentifrice, the TLBP will be simulated with the positioning in two points: one in the center of the middle third and the other in the cervical third, without laser light emission, and the sound of the equipment will be mimicked with the Beep application (Foncannon Inc, Google, © 2018).

The placebo group will receive the same protocol as the CPP-ACPF group, but the gel used will be a water-soluble base with no active ingredient (K-Y®, Johnson & Johnson, SP, Brazil).

**6.7.2. Laser therapy and laser therapy associated with CPP-ACPF**

In the laser group, the laser will be applied using an infrared light spectrum with wavelength of 808 nm with its active medium AsGaAl, positioning the tip in two points, one positioned in the center of the middle third and the other in the cervical third. It will be used at each point 60 J / cm², for 16 seconds, using Photon Laser III Therapeutic (DMC Equipamentos, São Carlos, SP, Brazil, Ltda). Before application of the laser, the placebo gel will be applied as previously described.

In the laser + CPP-ACPF group, CPP-ACPF will be applied following the same protocol of G. CPP-ACPF, and then the laser will be applied in the same way as in the laser group.

## **6.8. Assessment of pain sensitivity**

For the evaluation of pain sensitivity, the visual analogue scale (EVA) of 10 cm in length will be used, where 0-pain is absent and 10-pain is extreme. Requesting the participant to signal the number compatible with the pain sensation after application of the stimuli, evaporative (triple syringe) and tactile (exploratory probe). Sensitivity assessment will be done in five moments: Immediately before starting treatment, after the first session, after the second session, after the third session and after one month of treatment.

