**RESEARCH PROJECT**

**3 – INTRODUCTION**

Dentin hypersensitivity (HD) is defined as: "Acute and short-lived pain from exposed dentin on a thermal, evaporative, tactile, osmotic or chemical stimulus, and which cannot be attributed to any other form of dental defect or pathology ". (1,2,3) The reported pain is of short duration and is remission when the stimulant is withdrawn, affecting the patients' quality of life, which can compromise daily activities such as brushing teeth, eating, drinking, and even social interaction. (4,5)

Non-carious cervical lesions (LCNC) are characterized by the irreversible loss of cervical tooth structure at the cement-enamel junction level (JCE). Among the etiological factors of these lesions we have stress, biocorrosion and friction, and according to the factor that predominates in their development the LCNC are divided into: Abfraction that results mainly from the occlusal trauma that produces tensions in the JCE, generating microfractures in the enamel and dentin exposure. Dental brushing, associated with biocorrosion due to changes in diet, produces tooth wear. (2,6) Because of the irreversible loss of cervical tooth structure that originates, any LCNC could be linked to the development of HD. (7)

Loss of gingival-tooth bonding or gingival recession is another factor related to the exposure of the dentinal tubules at the cemento-enamel junction. Since the rate of cement resorption is greater than that of dentin, a root exposure increases, increasing the probability of opening the dentinal tubules to the oral medium, this whole cycle results in HD. (8)

The hydrodynamic theory of Brännström is accepted to describe the origin of HD, which is initiated by thermal, mechanical or chemical stimuli acting on the exposed dentin tubules, altering the movement of the fluid inside them and stimulating the response of the fibers A-β and A-δ (which are surrounding the odontoblasts), which react in the form of pain. (1,2) According to this theory, the best treatment for sensitivity is the reduction of fluid movement within the tubules by obstructing them, or by limiting the nerve response. (9)

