The ideal desensitizing material should exhibit rapid action, long-term effect, be biocompatible, non-irritating to the pulp, painless, easy to apply, and not cause tooth color change. (10,11) The fluorinated amorphous calcium casein-phosphate (CPP-ACPF) phosphopeptide may be useful in reducing HD because of its ability to incorporate into the surface of the enamel and dentin, acting as a reservoir of calcium and phosphate, occluding the dentinal tubules, avoiding the movement of liquid inside them, preventing the stimulation of the nerve fibers, and therefore the HD. (12)

Casein phosphopeptides (CPP) originate by enzymatic hydrolysis of casein. CPP has multiple phosphoserine residues, which interact and bind to calcium and amorphous phosphate (ACP) ions stabilizing them in an aqueous solution, forming the CPP-ACP complex. When fluoride is added, it becomes phosphopeptide of casein-fluorinated amorphous calcium phosphate (CPP-ACPF), which is more effective than CPP-ACP to inhibit enamel demineralization and facilitate remineralization of enamel early lesions by the availability of high concentrations of calcium and phosphate. (13,14)

Low power laser therapy (TLBP) involves the noninvasive application of red light (600-700 nm) and near infrared (700-950 nm), with a power density (irradiance) between 01 mW and 5 m W / cm2, (15) being increasingly employed in medicine and dentistry due to its analgesic, anti-inflammatory and biostimulating effects. It acts by inducing the production of mitochondrial adenosine triphosphate (ATP), increasing the presence of β-endorphin, and by inhibiting the enzyme cyclooxygenase, which transforms arachidonic acid into prostaglandins, attenuating the perception of painful stimuli in dentin tissues. (16) TLBP also reduces dentin sensitivity by means of photobiomodulation of the dental pulp, generating an increase in the cellular activity rate of odontoblasts, increasing its production of tertiary dentin, thus obliterating the dentinal tubules. (17,18)

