When CPP-ACP and a placebo gel were evaluated, under the effect of decreasing HD during 6 months, CPP-ACP demonstrated a rapid and stable reduction of HD during follow-up, whereas placebo generated an improvement moderate, but this was not statistically significant. (36) This is in agreement with Tung et. Al 1992, which demonstrated that, at high concentrations, CPP-ACP precipitates amorphous calcium phosphate, which, being the main inorganic component of the tooth, decreases dentin permeability by 85%, acting as an excellent tubular obliterator. (36)

On the other hand, TLBP has been applied to promote wound healing, reduce inflammation, and alleviate chronic and acute pain. This latter effect is related to the suppression of the activity of the substance P and bradykinin, serotonin release, improved circulation reduction in the production of acid metabolites that stimulate pain receptors, and deceleration of the action potential velocity, inhibiting the electrical conduction of Fibers C and Aδ, and modulating the pain threshold. However, the therapeutic effects of TLBP are subject to the application of certain wavelengths, laser intensity, location and optical properties of treated tissues. (15)

The diode laser of arsenic gallium and aluminum (AsGaAl), with a wavelength of 810 nm, increases the action potential of nerve cells, thus limiting the transmission of painful stimuli, but without heating the dental surface to the degree of generating modifications in the same. (37) With other wavelengths, the increase in energy in the dental surface leads to dentin fusion, and reduction of the diameter or obliteration of the dentinal tubules. (9, 38) A recent systematic review has shown that AsGaAl laser is more effective in reducing HDD in the long term than certain desensitizing agents without causing pulpal damage, allergy, or obvious clinical complications. (21)

However, although there are multiple treatments to reduce HD, none of them are considered a "gold standard", since the most commonly used desensitizing agents are effective in the short term, with an unstable response rate in more extended times (39,40) the need for clinical trials to evaluate the effectiveness of desensitizing treatments over time and to clarify the methodology and ideal product for the treatment of this disease due to the impact on the quality of life of its patients.

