**Table 01: Selection criteria.**

| - INCLUSION CRITERIA | | ^x^ EXCLUSION CRITERIA |
| --- | --- | --- |
| - Presence of dentin exposure in anterior and / or posterior teeth - presence of two to four teeth with hypersensitive dentin, with a response ≥04 on the 10 cm long visual analogue scale (VAS). - Non-carious shallow lesion up to 2 mm deep, according to the Smith & Knight index (measured with a millimeter probe). (42) - Class I gingival recession according to Miller's classification. (43) | - Milk protein allergies; - Systemic diseases; - Presence of pulpitis; - Carious lesions; - Presence of parafunctional habits. - Presence of restorations in the cervical area, or defective in the tooth; - Presence of periodontal disease; - Presence of cracks or fractures in the enamel; - Patients in fixed orthodontic treatment; - Pregnant or lactating women; - Medication with analgesics; - Desensitizing treatment during the three months prior to the research recruitment date. | |

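### Pulpitis, analgesics and other desensitising treatment are screened at entry but not recorded afterwards, and no visit records harms, so an affected VAS score could not be recognised and nothing could be reported on safety.

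*Protocol*

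**What the plan says.** Section 3 of the protocol defines dentin hypersensitivity as brief stimulus-evoked pain "which cannot be attributed to any other form of dental defect or pathology". Table 01 applies that definition at selection. Its exclusions include "Presence of pulpitis" and "Medication with analgesics", and desensitising treatment in the three months before recruitment.

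After entry, Section 6.8 sets five assessments: "Immediately before starting treatment, after the first session, after the second session, after the third session and after one month of treatment". Each consists of a VAS score after an air stimulus (6.8.1) and after a probe stimulus (6.8.2). Section 6.8.3 adds the quality-of-life questionnaire at baseline and one month, and a questionnaire on diet, systemic disease and parafunctional habits for a regression analysis. Section 6.9 analyses the sensitivity values as the participants report them.

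Section 6.4 gives each participant a soft toothbrush, a dentifrice without desensitising action and brushing guidance, with the declared purpose of limiting interference during follow-up. Section 6.1 says that participants are told about risks.

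**The concern.** A VAS score after an air jet or a probe measures pain. By the protocol's own definition it measures hypersensitivity only while other causes of pain, and other treatments that change pain, are absent. The protocol secures this at entry and then stops looking. Section 6.4 shows that the authors regard interference during follow-up as a real possibility, yet nothing records whether it occurred.

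Two things are at stake:

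- **Reading the one-month VAS.** A score altered by an analgesic, another product or pulpal pain would be indistinguishable from a response, or non-response, to the study treatment.
- **Harms.** The trial tests a combination of two active treatments and would end with no information on adverse events for either treatment or for the combination.

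This is not a matter that can wait for a statistical analysis plan. An analysis plan can say how to use such data, but it cannot recover data that no visit collected.

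**Working it through.** **Step 1. Entry criteria set against post-entry records.**

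| Item | At entry (Table 01) | After entry (Sections 6.4, 6.8 to 6.8.3) |
| --- | --- | --- |
| Pulpitis | Excluded | Not recorded |
| Analgesics | Excluded | Not recorded |
| Other desensitising treatment | Excluded for the preceding three months | Kit supplied, use not verified; other products not recorded |
| Adverse events | Not applicable | Not recorded |

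The Section 6.8.3 questionnaire covers systemic disease and parafunction, which are also Table 01 exclusions. It covers none of the rows above. The risk information in Section 6.1 is given to participants before treatment and is not a record of harm.

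**Step 2. Direction of any bias.** An analgesic or another desensitiser would lower a VAS score. Pulpal pain would raise it. The effect on a comparison of an active arm with placebo depends on where it happens:

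- lowered scores in placebo, or raised scores in the active arm, shrink the difference;
- lowered scores in the active arm, or raised scores in placebo, enlarge it.

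The documents give no frequency for any of the four cases, so neither the sign nor the size of a bias can be derived.

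**Step 3. When it could arise.** Section 6.7 places three sessions 24 hours apart, so the first four assessments span about 2 × 24 = 48 hours. The fifth follows at one month. The exposure that matters most is the interval before that last reading.

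**Step 4. What a harms record could show.**

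- *Participants per arm.* Section 6.5 plans about 10 blocks of four, with one participant per arm in each block, so about 10 × 1 = 10 per arm. This agrees with 20 teeth per group (Section 6.3) at the minimum of two teeth each: 20 / 2 = 10. Two arms receive the laser, so about 20 participants are laser-treated; the same holds for the paste.
- *Formula.* With zero events in n participants, the one-sided 95% upper limit for the event probability is 1 − 0.05^(1/n).
- *One arm, n = 10.* 1 − 0.05^(1/10) = 25.9%.
- *Both laser arms, n = 20.* 1 − 0.05^(1/20) = 13.9%.
- *If the 20% loss in Section 6.3 applied to participants.* One arm has 10 × 0.8 = 8, giving 1 − 0.05^(1/8) = 31.2%. Two arms have 16, giving 1 − 0.05^(1/16) = 17.1%.

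Without a harms record, no such limit can be calculated.

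**The case against.** The strongest case against the point is that the scenarios are unlikely here. Four of the five assessments fall within about two days. Section 3 describes the pain as short and ending when the stimulus is withdrawn, which gives little reason for routine analgesics. Section 4 cites a systematic review in which this laser type worked "without causing pulpal damage, allergy, or obvious clinical complications". Table 01 excludes milk-protein allergy, the evident allergy risk of a casein product, and Section 6.4 supplies a neutral dentifrice. Section 5 sets no safety objective, and so few participants would say little about safety anyway.

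Much of this stands, and it rules out several stronger readings that a reader might infer:

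- *That the one-month VAS fails to measure hypersensitivity.* Nothing shows that masked or pulpal pain occurs. The consequence is conditional.
- *That bias would arise mainly in placebo.* Placebo participants receive a gel in matching containers and a simulated laser with sound (Sections 6.6 and 6.7.1). No passage suggests that they would turn to other remedies more often.
- *That the protocol itself names the harms to be expected.* The Section 3 phrase "be biocompatible, non-irritating to the pulp, painless, easy to apply, and not cause tooth color change" describes an ideal material, and the Section 4 review reports that harms were absent.
- *That every tooth-level exclusion should be re-examined at each visit.* "Carious lesions" and "Presence of cracks or fractures in the enamel" are reasonable at entry. Repeating those checks about a day apart would add burden for little gain.
- *That an emerging problem would go unnoticed.* The evaluator stimulates the study teeth at every assessment. What is missing is a place to record what is found.

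What does not stand is the conclusion that nothing need be done. A review of other patients does not replace observation of this combination, the kit does not address analgesics, and unlikely events still have to be recorded if they are to be ruled out.

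**Conclusion.** The point holds in a limited form. The protocol screens for pulpitis, analgesics and recent desensitising treatment at entry, records none of them afterwards and has no harms record. The supplied dentifrice is a partial control whose use is not verified. If a score were affected, it would be analysed as hypersensitivity with no means of detecting it. I put no size or sign on that bias, because the documents supply no frequency for it.

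The loss of harms information does not depend on those scenarios. The trial could report nothing on harms of the laser, the paste or their combination. With recording, zero events would still leave upper limits of about 26% for one arm and 14% for the two laser arms together. These assume about 10 participants per arm, full follow-up and independent participants.

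This is an inexpensive improvement to data collection. It does not show that the efficacy comparison is invalid.

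**What to change.** At each post-baseline assessment already scheduled in Section 6.8, have the blinded evaluator complete a short form recording:

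- any adverse event, including spontaneous or lingering tooth pain, soft-tissue or allergic reaction, and colour change;
- analgesic use in the preceding 24 hours, and any other desensitising product used since the last visit.

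Report events by arm and per participant. Keep all readings in the main comparison, so that it stays a comparison of the randomised groups. Add one sensitivity analysis that leaves out readings taken under analgesics or other desensitisers, and readings from teeth with a diagnosed other cause of pain. It will not remove a bias from the main result, but it will show whether the conclusion depends on the affected readings.

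The cost is a one-page form, slightly longer visits and one extra analysis, with no added visit or staff. The harms data will remain imprecise at this sample size and should be reported with their limits.

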### **6.8.1. Evaporative Stimulation**

### The evaporative stimulus will consist of the application of a 40 psi air pressure of the triple syringe for 03 seconds, being directed perpendicular to the vestibular face of the tooth at a distance of 0.5 cm, the pain response will be measured by the participant according to the EVA . (44)

### **6.8.2. Tactile Stimulus**

### The tactile stimulus will be realized from the contact of the exploratory probe in the form of cross. The contact will be performed vertically in the cervico-incisal direction and horizontally in the mesio-distal direction, in the cervical region of the hypersensitive teeth. And the HD degree will be recorded with the help of EVA. (44)

### **6.8.3. Dentin Hypersensitivity Experience Questionnaire (QEHD).**

### Participants will be given a questionnaire prior to the start of treatment, and after one month thereafter, to assess the impact of desensitizing treatment on their quality of life. The questionnaire is based on the model described by Boiko et. Al. (45) according to the Portuguese adaptation of Douglas-De-Oliveira et. Al. (46). Also, dietary habits, systemic diseases and parafunctional habits of the participants will be recorded through a questionnaire, in order to analyze through a regression analysis the possible interaction of these factors with the HD reported throughout the study.

## **6.9. Statistical analysis**

### The values ​​corresponding to the sensitivity reported by the participants were tabulated in an Excel spreadsheet (Microsoft Windows, 2010) and analyzed with the IBM SPSS Statistics for Windows 22.0 program (IBM Corp., New York, United States). Considering the parametric data of this study, if it has normal distribution of the same to the intergroup analysis will be done with mixed ANOVA, and the specific intergroup comparison will be done with the Tukey post-hoc test. If the data are abnormal distribution the intragroup comparison will be performed from the Friedman test and the intergroup by the Wilcoxon test. A significance level of 5% will be set for all analyzes to be performed.

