**6.3. Sample Calculation**

To determine the sample size of the study, data from a pilot study that followed the methodology proposed in this research project was used, with four participants, three (75% of the sample) being female and one (25% of the sample) of the sample. male, with mean age of 31 years and standard deviation of ± 1.91. In the pilot study, 16 teeth were randomly assigned to one of the four groups with the Research Randomizer Calculator (www.socialpsychology.org/randomizer.htm).

The VAS was used to measure sensitivity, considering a clinically relevant difference of three units between the initial and final VAS scores, according to a previous study (20). The G Power® program (Heinrich-Heine-Universität Düsseldorf, Germany) was used for mixed ANOVA, considering a statistical power of 80%, α error of 5% and prediction of sample loss at the end of the study of 20%. The resulting sample for this study was 80 teeth, 20 teeth per group.

[figure not shown]

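### Section 6.9 leaves the main VAS analysis undetermined until the outcome data are seen, and its two routes are not equivalent

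*Protocol*

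**What the plan says.** Section 6.9 of the protocol sets a two-way rule for the VAS scores. The first route is conditional: "if it has normal distribution of the same to the intergroup analysis will be done with mixed ANOVA", followed by Tukey comparisons. The second reads: "If the data are abnormal distribution the intragroup comparison will be performed from the Friedman test and the intergroup by the Wilcoxon test". It adds that "A significance level of 5% will be set for all analyzes to be performed". The section does not name a normality test or its level. It does not say what is tested (raw scores by arm and moment, pooled scores or residuals), or what happens if one moment or stimulus passes and another fails.

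Section 6.3 sizes the trial for the first route only. The software "was used for mixed ANOVA, considering a statistical power of 80%, α error of 5"%, with 20% loss, and the result is 80 teeth, 20 per group.

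Three design features bear on the shape of the scores:
- Table 01 admits teeth "with a response ≥04 on the 10 cm long visual analogue scale (VAS").
- Section 6.8 bounds the scale at 0 and 10 and describes the reading as "Requesting the participant to signal the number compatible with the pain sensation".
- Section 6.3 targets a fall by "considering a clinically relevant difference of three units between the initial and final VAS scores".

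**The concern.** A confirmatory analysis should be fixed before the outcome is seen. Here the outcome data choose the analysis, and the choice changes more than the test statistic.

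- **Question answered.** A mixed ANOVA of arm by moment tests whether the course of pain differs between arms, which is the null in section 5. Friedman tests change over time inside one arm. Wilcoxon compares two samples. Neither tests arm by moment.
- **Error control.** Tukey covers the pairwise comparisons in the first route. Nothing covers them in the second.
- **Sizing.** The stated power describes only one of the two analyses that may be run.

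The gate is also a poor guide to whether the ANOVA is sound. The model needs roughly normal residuals, not normal raw scores, and scores pooled over arms and moments can look non-normal simply because treatment works.

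**Working it through.** **1. The plan's own figure.** The 80 teeth cannot be reproduced, because section 6.3 gives no VAS standard deviation, effect size f or correlation. Working backwards, 20 per group less 20% loss is 20 × 0.8 = 16 evaluable, and 4 × 20 = 80. A two-mean calculation for a 3-unit difference (80% power, 5% two-sided) gives 16 evaluable per group at an assumed SD of 3.0. Assumed SDs of 2.0 and 2.5 would give totals of 36 and 56. So the figure is attainable, but only under an SD that the protocol does not state, and only for the parametric route.

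**2. Multiplicity in the fallback.** Four arms give 4 × 3 / 2 = 6 pairwise comparisons. At 5% each, treated as independent, the familywise error is 1 − 0.95^6 = 0.265 at a single moment for a single stimulus. The six tests share arms, so the true value is lower; about 26% is an upper figure.

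**3. Why a switch is possible.** A tooth entering at the minimum of 4 that falls by the target 3 units ends at 4 − 3 = 1, one unit above the floor. The entry cut and the scale bounds both push raw scores away from a normal shape.

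**4. How likely a switch is.** Section 6.8 has five moments, so each stimulus has 4 × 5 = 20 arm-by-moment cells. If each cell were tested at 5%, exactly normal data in independent cells would fail at least once with probability 1 − 0.95^20 = 0.64.

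The table gives simulated failure rates of a Shapiro-Wilk test at 5%. Everything in it is assumed: the test and its level, parent baseline means of 5 to 7, SDs of 1.5 to 2.5, falls of 3 to 5 units in the active arms, and 16 or 20 teeth per arm. Baseline is cut to 4–10 and later scores are clipped to 0–10. Each scenario had a few hundred runs, so the second decimal is loose.

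| What is tested | Continuous scores | Whole-number scores |
| --- | --- | --- |
| Raw scores, any of 20 cells fails | 0.53–1.00 | 0.96–1.00 |
| Baseline pooled over arms | 0.05–0.95 | about 1.00 |
| One-month scores pooled over arms | 0.04–1.00 | 0.44–1.00 |
| Model residuals | 0.03–0.12 | 0.03–0.18 |

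The entry cut matters less if the analysed baseline is a separate reading from screening. With an assumed screening-to-baseline correlation of 0.6 to 0.8, rejection for pooled continuous baseline scores falls to about 3–30%.

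**5. Whether the gate is needed.** One-month scores were simulated with clipping at 0 and 10 and with 16 or 20 independent teeth per arm. One-way ANOVA had a type I error of 4.5–5.8%. Kruskal-Wallis, standing in for a between-arm rank test, had 4.3–5.1%. With placebo 2 units worse, power differed by at most about 5 points (0.62 against 0.57 at 16 per arm; 0.73 against 0.69 at 20 per arm). In these scenarios the gate protects nothing.

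**The case against.** A reader might infer that the check is likely to fail, so that the mixed ANOVA will probably not be run. The documents do not support that.

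- Section 6.9 does not say what is tested. If residuals are tested, failure is uncommon (3–18%). The test and its object are also details that a statistical analysis plan may supply.
- The cut at 4 is an eligibility rule. Section 6.8 takes the analysed baseline immediately before treatment, section 6.4 plans a prophylaxis to standardise the starting condition, and section 7 schedules screening ahead of the trial. If the readings are separate, baseline is not strictly cut at 4. Table 01 also does not say which stimulus must reach 4.
- Section 6.8 asks for a number on a 10 cm scale, which does not establish whole-number recording. Much of the high failure rate comes from rounding and from testing many cells, not from the entry rule or the floor.
- All means and SDs are assumed.

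These arguments stand, and they remove any claim about probability. Nor can it be said that the fallback loses much power, since rank and parametric power were close at one month. They do not remove the rule itself. The protocol states it, it acts on outcome data, and its branches differ in question and in error control however often the switch occurs.

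**Conclusion.** The point holds as a defect of specification. Until the outcome data are seen, the main VAS analysis is one of two non-equivalent procedures. Only one tests arm by moment, controls pairwise error and is covered by the sample size statement. The familywise error in the other could reach about 26% per moment and stimulus, if six unadjusted pairwise tests are run and treated as independent.

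A switch is a real possibility, but its probability is not determined by the protocol. It ranges from about 3% (residuals, or continuous baseline scores read separately from screening) to nearly 100% (raw scores tested cell by cell, low post-treatment scores pooled, or whole-number scores). This should be corrected, but it does not invalidate the design.

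**What to change.** Delete the normality condition in section 6.9 and name one primary analysis for both the air and the probe stimulus:

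- Use a repeated-measures mixed model of arm by moment, whatever the distribution of the raw scores. Include a participant-level term, because section 6.5 randomises participants and each contributes two to four teeth.
- Examine residuals for information only, with no switch of the primary analysis.
- As the robustness check, report a permutation test that re-shuffles participants' arm labels within the randomisation blocks. Section 6.5 plans about 10 blocks of four, and each block has 4! = 24 arrangements, so there is ample room for it.
- Keep rank tests only as a labelled sensitivity analysis.

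The cost is a rewording and a little more analysis work. Dropping the gate leaves the 80 teeth unchanged. Whether 80 teeth are enough once teeth are nested in participants is a separate question, which section 6.3 gives no correlation to answer. The downside is reliance on approximate normality of arm means with about 10 participants per arm (about 10 blocks, one per arm in each), which the permutation check covers.

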**6 – METHODOLOGY**

## **6.1. Ethical aspects**

This research project will follow the recommendations of the CONSORT (Consolidated Standards of Reporting Trials), (41). The research participants will be duly informed and informed about the risks, methods and objectives of this project. It is necessary to sign the informed consent form (TCLE) in accordance with the Helsinki declaration before starting treatment.

The information to be collected was exclusively scientific and the identity of the participants was preserved throughout the study. Participation in the study could be canceled and the consent term withdrawn at any time from the research, ensuring confidentiality of the participant even in case of abandonment of the treatment.

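### On the normal-data branch, the mixed ANOVA fixed in section 6.9 would, as usually run, drop every tooth missing one of five assessments, although 20% loss is expected

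*Protocol*

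**What the plan says.** Protocol section 6.8 schedules the VAS ratings: "Immediately before starting treatment, after the first session, after the second session, after the third session and after one month of treatment". Section 6.7 puts three sessions 24 hours apart, so the first four ratings fall within days and the fifth about a month later. Each rating is taken for an evaporative and a tactile stimulus.

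Section 6.3 plans with "prediction of sample loss at the end of the study of 20" per cent, and concludes: "The resulting sample for this study was 80 teeth, 20 teeth per group".

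Section 6.9 names SPSS 22.0 and splits the analysis by distribution. If the data are normal, "the intergroup analysis will be done with mixed ANOVA, and the specific intergroup comparison will be done with the Tukey post-hoc test". If not, Friedman serves the comparison within groups and Wilcoxon the comparison between groups.

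The protocol states no rule for incomplete rows. Section 6.1 allows withdrawal at any time and adds only "ensuring confidentiality of the participant even in case of abandonment of the treatment".

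**The concern.** A classical mixed (split-plot) ANOVA, read as the SPSS repeated-measures GLM, works on complete rows. The row here is a tooth with five values. A tooth rated before treatment and after all three sessions, but not at one month, leaves the model with its four observed values, and the Tukey comparisons use the same reduced set. A participant who does not return takes out all of their teeth, normally two to four (section 6.2).

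Two things are at stake. First, recorded data from the treatment days go unused, although the null hypothesis in section 5 covers the whole month. Second, the between-group test describes the teeth of those who completed, not of all those randomised. If return depends on the pain felt earlier, and pain differs between arms, the completers differ selectively between arms.

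**Working it through.** **Inputs from the protocol**
- 80 teeth, 20 per group, 20% loss (section 6.3)
- five moments (section 6.8)
- mixed ANOVA with Tukey, SPSS 22.0 (section 6.9)

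**Step 1. The stated sample and the loss.** The loss step fits a pre-loss sample of 64: 64 / (1 − 0.20) = 80, or 16 / 0.80 = 20 per group. The 64 itself cannot be rebuilt, because the readable text gives no SD, effect size f or correlation between repeated measures. Some assumed inputs reach it: an interaction effect of f = 0.20 with five moments and correlation 0.3 gives 64. Others do not: at the same correlation, f = 0.10 gives 248 and f = 0.40 gives 20. So 64 is consistent with the plan but not verified.

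**Step 2. Teeth in the complete-case test.** Loss = 0.20 × 80 = 16 teeth. Remaining = 80 − 16 = 64, about 16 per group if loss is even.

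**Step 3. Observed values discarded, per stimulus.** The 64 complete teeth give 64 × 5 = 320 values. If each lost tooth has k observed moments, the discarded share is 16k / (320 + 16k).

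| Last rating of the lost teeth | k | Discarded / observed | Share |
| --- | --- | --- | --- |
| Before treatment | 1 | 16 / 336 | 4.8% |
| After session 1 | 2 | 32 / 352 | 9.1% |
| After session 2 | 3 | 48 / 368 | 13.0% |
| After session 3 | 4 | 64 / 384 | 16.7% |

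The month-long gap before the fifth rating makes the last row plausible, but the protocol does not say when loss is expected. With two stimuli, the last row is 64 × 2 = 128 values.

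**Step 4. Could completers give a biased difference?** Only under assumed inputs. Both illustrations below treat ratings as independent between teeth and let loss depend on the rating after session 3.
- *Illustration A.* Means 6 and 3 both after session 3 and at one month; between-tooth and within-tooth SD 1.5 each, so total SD √(1.5² + 1.5²) ≈ 2.1. The log-odds of loss are −3.6 + 0.45 × VAS, giving 32% loss in one arm and 13% in the other. The completers' difference is 2.85 against 3.0 with full data, about 5% too small.
- *Illustration B.* One-month means 4.5 and 2.5 with ratings held within 0 to 10, SD 2, correlation 0.5 or 0.7, 20% loss overall. Full data give 1.90 to 1.92. Completers give 1.76 to 1.81 with a log-odds slope of 0.5 per VAS unit and 1.62 to 1.70 with a slope of 1.0, roughly 5% to 15% too small. With slope zero they give 1.92, which is no bias.

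If satisfied participants are the ones who stay away, the direction reverses.

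**The case against.** **Deletion is not in the protocol.** No section mentions listwise deletion, completers or an analysis set, and a rule for missing data may sit in an analysis plan that is not shown. This stands as a limit on the wording: deletion is how the named procedure usually behaves. It does not remove the point, which is that the protocol commits to a method that handles its own predicted loss poorly.

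**The non-normal branch is different.** A reader might infer that Friedman confines the between-group comparison to complete rows as well. It does not: section 6.9 gives Friedman only the comparison within groups. A Wilcoxon comparison between groups at each moment uses every tooth rated then. At one month it still sees only those who returned, but it does not throw away early ratings.

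**Withdrawals do not lose all their data.** They leave one model on one branch. Their values can still enter summaries, per-moment tests and the regression described in section 6.8.3.

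**Power may already be covered.** If 64 was the pre-loss figure, a test on 64 complete teeth is what the trial was sized for. This stands: the point is not that the trial is underpowered.

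**The bias is not shown.** Nothing in the protocol says that return depends on pain. In both illustrations loss depends on an observed rating, so a model using earlier ratings would recover the difference by construction. The shifts, about 0.1 to 0.3 VAS units, are also small beside the three units that section 6.3 calls clinically relevant.

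**Follow-up after stopping.** A reader might infer from section 6.1 that participants who abandon sessions are not assessed again. Section 6.8 does not make the one-month rating conditional on completing the sessions, so this is at most missing detail.

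**Conclusion.** The point holds for the normal-data branch. Under the usual repeated-measures GLM reading, and with no other rule in force, the between-group test would use about 64 of 80 teeth and discard between 4.8% and 16.7% of the observed VAS values per stimulus, the upper end if all loss follows the third session. The counts rest on the protocol's own 20% and five moments.

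The test is open to completer bias if return depends on earlier pain. Its size and direction are unknown, and there is none if loss is unrelated to response. A reader might infer that the planned comparison is necessarily biased, or that both branches of section 6.9 compare completers only; the protocol supports neither. This is a cheap improvement to a named method, not a flaw that invalidates the design.

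**What to change.** In section 6.9, replace the mixed ANOVA with a likelihood-based linear mixed model (SPSS MIXED) of VAS on arm, moment and arm-by-moment, with a random effect for participant and repeated measures within tooth. The participant term is needed because section 6.5 allocates participants, while each contributes two or more teeth; without it, teeth in one mouth would count as independent. State how pairwise comparisons between arms are adjusted, since the Tukey step is tied to the ANOVA being replaced.

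Analyse all study teeth of randomised participants in their allocated arm, using every available moment. Report the complete-case mixed ANOVA as a sensitivity analysis.

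The cost is revised wording in section 6.9 and slightly more modelling work in the same package, with no added participants or visits. The downside is reliance on missing-at-random given the observed ratings, which is generally weaker than what a completers' analysis needs but cannot be verified from the data.
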